## Abstract

**Background:**

Individuals receiving means-tested benefits are at a higher risk of being diagnosed with a psychiatric illness compared to those who are employed, and the rate of those working in the first labor market is low. The intervention (Individual Placement and Support, IPS) aims at maintaining or regaining working ability and at facilitating reintegration into the (first) labor market following a “first place, then train”-approach. The objective of the study is to conduct the first RCT in Germany that addresses a broad group of long-term unemployed individuals with severe mental illnesses that receive means-tested benefits, and to test the effectiveness of the IPS intervention.

**Methods:**

In this randomized controlled trial, about 120 eligible participants aged between 18 years and local retirement age will be randomly allocated to an intervention group (IG) or to an active control group (CG) using a parallel arm design. The IG will receive IPS + high quality treatment as usual (TAU), the active CG will receive TAU + a booklet on integration measures. A block-randomization algorithm with a targeted assignment ratio of 1:1 for participants in IG and active CG will be used, stratified by sex and three age groups. Assessments will take place before the intervention at baseline (t0), and 6 (t1), 12 (t2), and 18 (t3) months later. Primary outcome will be the proportion of participants having worked at least 1 day in competitive employment since baseline, as assessed at t3. Secondary outcomes will be related to employment/ vocation and mental health. In addition, there will be a process evaluation. Treatment effects on outcomes will be tested using appropriate panel-data regression models, and acceptability, uptake and adherence will be evaluated using descriptive statistics and appropriate inference testing.

**Discussion:**

The results of this trial are expected to generate a better understanding of the efficiency, feasibility, acceptance, and relevance of the IPS intervention in a German setting. They could be a first step towards the implementation of the method and towards improving the situation of long-term unemployed individuals with severe mental health problems.

**Trial registration:**

German Clinical Trials Register (DRKS00023245), registered on 22.02.2021.

## Background

Work is an essential part of daily life, and it is especially important for individuals with mental health problems [1]. It does not only provide a certain level of financial security and time structure, but also facilitates social interactions and mental health. A review of meta-studies by Paul et al. [2] shows the connection between mental health and unemployment: 34% of unemployed individuals were affected by mental health problems, double the number of their employed counterparts. Already in 2006, cross-sectional studies demonstrated a negative connection between unemployment and wellbeing in all six dimensions, i.e., unspecific symptoms, depression, anxiety, psychosomatic symptoms, subjective wellbeing, and self-esteem [3].

For a long time, there was no information available on how many of those receiving means-tested benefits in Germany also suffered from mental illnesses. In 2013, a study [4] provided this information using data from six different health insurance companies. It shows that 37% of insured individuals that received means-tested benefits were diagnosed with at least one psychiatric disorder, and that psychiatric diagnoses were on the rise. More than a fifth received a diagnosis in the area of “neurotic/ stress/ somatoform disorder”, and about every sixth was diagnosed with an affective or an addictive disorder. Schizophrenia, personality disorders, and behavioral disorders were much rarer. In 2009, about one out of seven individuals receiving means-tested benefits experienced depressive episodes, followed by somatoform disorders (1 out of 10). In addition, anxiety disorders, reactions towards heavy strain, and adjustment disorders played a role.

While there is a broad range of vocational (re) integration measures for people with mental illnesses in Germany, the rate of those working in the first labor market is low [5]. At the same time, the number of individuals with mental illnesses working in workshops for persons with disabilities is growing steadily, currently reaching 21% [6]. Many are also unemployed and receive benefits [4].

There seems to be much room for improvement regarding the cooperation between relevant stakeholders in healthcare, rehabilitation, and at jobcenters to support unemployed persons with mental illnesses [5]. In addition, new approaches are needed in the German rehabilitation system [7]. Until now, vocational integration efforts are selective and mainly tied to specific institutions with high entry barriers. Most of the time they follow an approach best described as “first train then place”, i.e., a preparatory training in a protected environment followed by the integration into the first labor market. Internationally, successful measures use individualized approaches with job coach support known as individual placement and support (IPS), and with the goal to quickly place an individual in the first labor market, i.e., „first place then train “ [8]. These approaches are also recommended by the S3 guidelines „Psychosocial therapies in severe mental illness [9]. Meta-analyses and reviews show that IPS is superior to traditional vocational rehabilitation in terms of achieving competitive employment and with regard to multiple other vocational outcomes like job tenure and total income [10, 11]. This holds also true in specific groups like people diagnosed with a psychotic illness [12], patients with offending histories [13], or young adults [14]. All of the previous trials were conducted outside of Germany, e.g. more recently in Norway [15] and the UK [16]. So far, only the multi-centric EQOLISE trial tested IPS in different European counties including a German study center [12]. Although the trial was in favor of IPS, results for the German study center were not significant. However, there was a tendency for participants in the IPS-group, as compared to those in the control group that received an alternative rehabilitation measure, to gain employment more often, work more hours and days, and keep employment for a longer duration [17]. Although the trial was powered for the multi-centric overall result, this discrepancy provoked national discussion [18].

We therefore want to fill a gap in research by conducting the first RCT in Germany that addresses a broad group of individuals with severe mental illnesses.

### Objectives

The objective of the LIPSY trial is to test the effectiveness of an IPS intervention in a German context, and with long-term unemployed individuals with severe mental illnesses that receive means-tested benefits. The intervention aims at maintaining or regaining their working ability and at facilitating their reintegration into the first labor market. We will test the hypothesis that IPS is superior to the treatment of the active control group (a booklet on integration measures). Specifically, we assume that participants will be significantly more likely to have worked in competitive employment for at least 1 day at t3 (18 months after intervention, primary outcome) if they received IPS (IG) as compared to not receiving IPS (CG). In addition, we will analyses the effects of the intervention on a wide range of vocational and health-related outcomes. Therefore, the present study closes a research gap in Germany, and if proven effective may further close a supply gap for reintegration of individuals with severe mental health problems.

## Methods

### Design and setting

The study will implement a randomized controlled trial (RCT) using a parallel arm design with allocation of participants to either an intervention group (IG) or an active control group (CG). Both groups will receive high quality treatment as usual as a standard treatment at a clinic for psychiatry, psychosomatics and psychotherapy (TAU), with participants in the IG additionally receiving IPS, and participants in the active CG additionally receiving a booklet on current measures for vocational rehabilitation. The study will take place in a clinical setting in Leipzig, a major city in Eastern Germany. The trial was registered at the German Clinical Trials Register on 22.02.2021 (DRKS00023245).

### Inclusion and exclusion criteria

Participants will be included based on the following inclusion criteria: (a) receiving means-tested benefits (German: ALG 2); (b) severe mental illness (GAF ≤ 50) as a main diagnosis (ICD-10) excluding acute intoxication and delirium; (c) age 18+ years up to local retirement age; (d) an expressed moderate to strong desire/ wish to work; (e) being willing and capable of giving informed consent; and (f) receiving treatment at an outpatient psychiatric clinic. Participants will be excluded if they do not fulfill the inclusion criteria.

### Interventions

Participants from both groups will receive high-quality TAU, i.e. the standard treatment according to their needs by a multiprofessional team at the outpatient psychiatric clinic. This can include medication, psychotherapy and a wide set of optional psychosocial therapies, like social skills training. In addition, participants in the IG will receive IPS, and participants in the active CG will receive a booklet that gives an overview on measures for vocational rehabilitation. There are no restrictions with regard to concomitant care.

#### Intervention group

IPS coaching is focused on the individual needs and goals of participants, and it covers all phases of vocational orientation and goal development, job application, beginning to work, workplace adaption, job retention, job loss, and (re)orientation. If they want to, participants can involve a related person and/or their employers in the coaching process, and coaches can meet participants outside the hospital. In addition, coaches build up contacts to potential employers in general. There will be a basic documentation of meetings, talks and communication between coaches and participants including key issues and agreements. All coaches are part of the clinic team, received an online training with certification (https://ipsworks.org/index.php/training-courses/), and they work manual-based [19]. Coaches cooperate closely with physicians, social workers, and therapists.

The coaching starts with a planning phase in which the needs of participants are assessed in detail and personal goals are defined. Specific questionnaires can be used to explore potential goals, strengths, and experiences of participants; they may also address cognitive abilities, social competence, qualifications, and daily activities, depending on the needs of the participants. Besides starting a job or changing occupations the exploration may also yield other goals like the acquisition of new qualifications, the beginning of studies, or an apprenticeship. Goals will be written down in an objective agreement which includes statements on vocational preferences, companies that will be addressed, and participant’s needs.

In the intervention phase, goal achievement will be addressed, for example, employers could be contacted. It is important that the intervention phase starts early, best in the first 30 days after the beginning of the coaching process. Once the participant has managed to start work/ training/ studies (integration phase), the coaching will be adapted to this new situation. For example, job coaches can then give the following support: meeting with family members to explore job-related strengths and goals; meeting with job center staff to coordinate planning; job search and preparation of job interviews; time management; social skills training; communication with the employer, e.g., for conflict mediation or workplace adaption; workplace coaching; group sessions with other participants.

The productive contact with employers is a crucial success factor. Therefore, it will be discussed at an early stage if, and in which form, it could make sense for participants to reveal their illness to their potential employer. Participants’ preferences with regard to the disclosure of their mental health status by their coach to a potential employer will be documented and binding. If a participant decides to disclose their condition, the contact between coach and employer will be documented. The participant can withdraw their agreement at any time.

Participants will be coached steadily, if requested also after the project has ended. Continued support via the hospital’s own social services is available. Due to the close contact between coach and participant, potential barriers can be identified at an early stage and individual solutions can be developed. Should participants miss appointments or not follow agreements, coaches will actively seek contact for 8 weeks after the last contact. Participants can withdraw from the program at any time. In addition, the IPS-process includes multiple opportunities for participants to give feedback and shape the process, which are expected to contribute to intervention adherence.

#### Active control group

Participants in the active CG will receive TAU and a booklet since a pure control group with no intervention would be neither feasible nor legally or ethically acceptable. The booklet gives an overview on current measures for vocational rehabilitation for individuals with mental illnesses.

### Assessments

We will collect data on sociodemographic variables and a wide set of characteristics related to employment situation, educational activities, additional work rehabilitation measures, health, disability, treatment, participation expectancy, and desire to work via a study-specific questionnaire. For example, items address citizenship, health status (e.g., need for care), employment history (e.g., “How many years did you work in competitive employment?”), psychotropic medication, and psychotherapy.

In addition, psychologists from the clinic will perform a clinical diagnosis of participants. They will forward information on the diagnosis (ICD-10) and the global level of functioning (GAF) to the ISAP research team using the project-ID of participants. The presence of a severe mental illness (GAF ≤ 50) as a main diagnosis, excluding acute intoxication and delirium, is also a key inclusion criterion.

Perceived social support will be assessed via the short form of the *Lubben Social Network Scale (LSNS-6)*, containing six items that can be rated on 6-point Likert scales [20]. Attitudes toward recovery from psychiatric disorders will be assessed via the Recovery Attitudes Questionnaire (RAQ-7; seven items [21];). Participants will be asked for their subjective prognosis of gainful employment via the *“Subjektive Prognose der Erwerbstätigkeit”-Skala* (*SPE*, [22]) that contains three items which can be answered on a 5-point Likert scale. Loneliness will be measured with the 3-item SOEP-version of the *UCLA loneliness scale* (5-point scale [23, 24];). Optimism and pessimism will be measured with the revised version of the *Life-Orientation-Test (LOT-R)* via six items (5-point scales, filler items excluded [25, 26];). We will assess health care consumption in eight different areas, e.g., living situation, hospital stays, and medication, via a shortened version of the „Fragebogen zur Inanspruchnahme medizinischer und nicht medizinischer Versorgungsleistungen bei psychischen Erkrankungen “(FIMPsy, [27]). The 36-item *WHO Disability Assessment Schedule* (*WHODAS 2.0* [28];) will be used to measure general health and disability levels in six different domains (*cognition, mobility, self-care– hygiene, dressing, getting along, life activities, participation*) at t0, but we will remove four items related to work. At t3 the 12-item version of the instrument will be applied. In addition, we will use original items to measure substance use.

Cognitive performance will be assessed by trained staff at the clinic via the *SCIP-D* (*Screen for Cognitive Impairment in Psychiatry – German version* [29];), a brief screening tool to assess cognitive impairment in psychiatric patients in five areas (*immediate verbal learning, delayed verbal learning, working memory, verbal fluency, processing speed*).

### Primary outcome

Our primary outcome is the proportion of participants “having worked at least one day in competitive employment” (yes vs. no) during the entire observation period upon t3 (18 months after baseline). We define competitive employment as employment that any person can apply for regardless of disability status. Workers earn minimum wage or higher, and self-employment is also considered to be competitive employment (also see ipsworks.org). It will be assessed as self-reported information via questionnaire.

### Secondary outcomes

We will use items to assess vocational variables from t1 to t3, i.e., time until first competitive employment (days), job tenure (days), number of different employments, working time per week (hours), overall time in employment (days), reason for the termination of the first competitive employment (if applicable), current employment status and job position, current employment situation (e.g., permanent full time), and wage/ income.

The following instruments and items will be assessed at every time point, from t0 to t3. The general state of health will be measured with the *EuroQol* visual analogue scale (EQ-VAS) from the *EQ-5D* (e.g., [30]), a thermometer-like scale on which participants can rate their health from worst (=0) to best (=100) imaginable health. Physical and mental health will be assessed with the 12-item *Short-Form Health Survey (SF-12*, different scale formats [31];), and depressiveness with the *Patient Health Questionnaire-9 (PHQ9)*, which contains 9 symptom-oriented items that can be rated from 0 (= not at all) to 3 (= almost every day) [32–34]. In addition, we will use the *Mini-Symptom-Checklist* that includes three sub-scales with six items each (*Depression, Anxiety, Somatization*) and the 5-item *Aggression/Hostility*-subscale from the *Brief-Symptom-Checklist* which can be rated on 5-point Likert scales (*Mini-SCL, BSCL* [35, 36];). The 3-item *Alcohol Use Disorders Identification Test (AUDIT-C)* will be used to assess problematic alcohol consumption [37]. In order to measure participants self efficacy with regard to their return to work, we will use the 11-item *return-to-work self-efficacy scale* (*RTW-SE* [38, 39];).

The following instruments will be used at two time points, t0 and t3. The *Working Ability Index (WAI)* consists of seven dimensions that can be rated on different scales yielding end results between 7 (= critical working ability) and 49 (= very good working ability) points [40]. Since the *WAI* to a large extend addresses individuals that are working, we will utilize a reduced scale at t0. We will measure attitudes towards work (6 items) and working motivation/wish to change (2 items) with items from the “*Diagnostikinstrumente für Arbeitsmotivation*” (*DIAMO* [41];), and vocational self efficacy with the “*Skala zur Erfassung beruflicher Selbstwirksamkeitserwartungen*” (*BSW* [42];).

An overview of all variables, outcomes and other measures that will be implemented is shown in Table 1.

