### Sample size

Sample size calculation is based on the primary outcome measure (competitive employment for at least 1 day). In the IPS-literature there is only one European Trial with data from a German study center [12]. The proportions of the EQOLISE-Trial were applied in the power calculation (IG: 0.55, CG: 0.28). To detect a between-group effect of ∆ = 0.27 in favor of IG at 18 months, considering a significance level of α = 0.05 (one-sided) and a statistical power of 1 - β = 0.80, we estimated a target sample of *n* = 41 participants per arm is needed. Anticipating a drop-out rate of 30% until 18 months after baseline assessment based on experiences with previous clinical research projects, the total sample size would have to comprise roughly 60 individuals per group.

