### Statistical methods

All data will be examined with regard to potential inconsistencies and missing values. Missing information in variables will be inspected and addressed by using multiple imputation methods [43], if appropriate. In order to check for systematic differences between completers and non-completers we will perform a dropout analysis. In addition, we will check if there are systematic differences between IG and active CG with regard to sociodemographic, health-related and employment variables. Analyses on primary and secondary outcomes will be performed as intention-to-treat. In addition, we will also perform a “per-protocol”-analysis including all participants from the IG that completed the goal agreement and their first intervention and participants from the active CG. Treatment effects on primary and secondary outcomes will be tested using appropriate panel-data regression models including group, time, an interaction between group and time as predictors and adjusting for relevant covariates and baseline outcome measures. Acceptability, uptake and adherence with regard to the intervention will be evaluated using descriptive statistics.

For all analyses the level of statistical significance will be set to *p* < .05. The results of the study will be reported according to the guidelines of *the Consolidated Standards of Reporting Trials* (*CONSORT*) statement [44].

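### Time until first competitive employment does not fit the panel regression assigned to all secondary outcomes: it needs a time-to-event analysis, and job tenure among job-finders should not be tested between arms

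*Protocol article*

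**What the plan says.** The Secondary outcomes section names vocational variables collected from t1 to t3, among them "time until first competitive employment (days), job tenure (days), number of different employments, working time per week (hours), overall time in employment (days"). Unlike the health scales, these are not collected at t0.

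The Statistical methods section gives one model for everything: "Treatment effects on primary and secondary outcomes will be tested using appropriate panel-data regression models". The sentence goes on to fix the terms: group, time, their interaction, covariates, and the baseline value of the outcome. No outcome is exempted. The same section commits to intention-to-treat for primary and secondary outcomes and names multiple imputation, where suitable, for missing information. It mentions neither censoring nor how a participant who never starts a job enters the duration variables.

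The Sample size section supplies the expected rates of ever working: "The proportions of the EQOLISE-Trial were applied in the power calculation (IG: 0.55, CG: 0.28").

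**The concern.** A panel model needs repeated measurements of the same quantity. Time until first competitive employment is a single waiting time. For anyone without a job at t3, or at the last contact before dropout, it is known only to exceed the time observed. That value is censored. It is not missing in the sense that multiple imputation addresses, and filling it in from people who did find work would invent jobs.

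Job tenure has a related problem: without a job there is no tenure. A between-arm test among job-finders compares two subsets formed after randomisation by the outcome that the intervention is meant to change.

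At stake are the interpretability of two vocational outcomes and, for time to first job, the ability to detect an effect of the size the trial is planned on. The rule for the never employed can move the result considerably, so it should be fixed before unblinded data are seen.

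**Working it through.** **Inputs.** From Sample size: rates 0.55 and 0.28; "considering a significance level of α = 0.05 (one-sided) and a statistical power of 1 - β = 0.80"; 41 per arm; 30% dropout; about 60 per arm. From the assessment schedule: 18 months of follow-up, taken as 548 days. Assumption: constant hazards, varied below.

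**1. The plan's own figure.** With pooled variance and mean rate 0.415:

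n = [1.645·√(2·0.415·0.585) + 0.842·√(0.55·0.45 + 0.28·0.72)]² / 0.27² = (1.146 + 0.564)² / 0.0729 = 40.1, hence 41 per arm. Dropout: 41 / 0.70 = 58.6, hence 59. The stated 41 and roughly 60 are reproduced.

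**2. Can time to first job supply the model terms?**
- Time and group-by-time: no, there is one value per person.
- Baseline value: no, the variable is not collected at t0 and could not be.
- Complete value: no, it is censored at t3 or dropout.

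**3. Share without a first-job date at 18 months.** 1 − 0.55 = 45% (intervention) and 1 − 0.28 = 72% (control). Job-finders: 22.6 and 11.5 of 41 per arm, or 33 and 16.8 of 60 per arm. Dropout adds further censoring.

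**4. Implied effect.** λ = −ln(1 − p)/548: 0.001457 and 0.000599 per day. Hazard ratio = ln 0.45 / ln 0.72 = 2.43.

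**5. The same effect in days among job-finders only.** Mean = 1/λ − 548·(1 − p)/p:
- Intervention: 686.3 − 448.4 = 237.9 days
- Control: 1668.2 − 1409.1 = 259.0 days

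The difference is 21 days, against standard deviations of about 156 and 158 days.

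**6. Two-sided 5% power, 10,000 simulated trials.**

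| Never-employed participants | 41 per arm | 60 per arm |
|---|---|---|
| Dropped, t-test on days | 6.5% | 7.2% |
| Entered at 548 days, t-test | 62.7% | 78.8% |
| Censored, log-rank test | 71.9% | 87.0% |

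The 41-per-arm column stands for the number left after the planned dropout; the 60-per-arm column models no dropout. The Schoenfeld formula agrees for the last row: 34.0 events give 73.6% and 49.8 events give 88.0%. One-sided, the first row becomes 9.8% and 11.6%, and the last 81.1% and 92.9%. Imputing from job-finders was not simulated separately. It adds no information about the never employed, so it is treated like the first row.

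**7. Sensitivity to the hazard shape.** Weibull shapes 0.7 to 1.5 (8,000 runs each) leave the job-finder difference at 19 to 22 days, power after dropping at 6% to 8%, and power with 548-day coding at 60% to 81%.

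**The case against.** The strongest reply is that the protocol nowhere says the never employed will be dropped. Its intention-to-treat statement points the other way. A reader might infer from step 5 that a large effect on time to work would be nearly invisible under this plan. The documents do not support that: the result follows only if non-workers are excluded or imputed from workers. With 548-day coding, the loss against log-rank is about 8 to 9 percentage points. That part of the reply stands.

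A second reply is that the qualifier on the model could cover a discrete-time hazard model on the t1 to t3 periods, which is a regression with group, time and their interaction, and that an unseen analysis plan may settle the details. This stands in part: such a model would be acceptable. But the sentence as written also requires baseline adjustment, which this outcome cannot supply, and it exempts nothing. An analysis plan that got this right would have to depart from it.

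A third reply concerns scope. Weekly hours, number of jobs and total days employed have a natural zero for people without work and can be analysed in everyone; hours can even be a genuine repeated measure. A reader might extend the criticism to them, but it does not apply beyond the need to state the zero.

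Finally, one might argue that the intervention brings harder-to-place people into work, so its job-finders would look worse on tenure. Nothing in the protocol supports that direction, and its Background section cites better tenure with the intervention. The point about tenure needs only that the comparison is not randomised, whichever way selection runs.

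**Conclusion.** The concern holds for time until first competitive employment and, in a lesser way, for job tenure. The stated model does not fit the first, which is censored for about 45% and 72% of the arms at the planning rates. The size of the loss is conditional on the unstated rule: power of about 7% if the never employed are dropped or imputed from workers, and about 63% to 79% if they are entered at 548 days, against about 72% to 87% for log-rank. These figures rest on the planning rates, near-constant hazards, 548 days of follow-up, two-sided testing, and 41 to 60 per arm with no dropout modelled in the larger case.

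Severity is moderate. The primary outcome, ever having worked, is a yes/no variable that does not depend on having a job date. It is unaffected and captures much of the same effect.

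**What to change.** Amend the Statistical methods section as follows:

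- Exempt time until first competitive employment from the panel model. Analyse it in all randomised participants with cumulative-incidence curves and a Cox or discrete-time hazard model that uses the randomisation strata (sex and age group), censored at last contact or t3.
- Enter participants known not to have worked as 0 for weekly hours, number of jobs and total days employed. Keep imputation for periods whose employment status is unknown.
- Report job tenure among job-finders descriptively, without a between-arm test.

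The cost is one additional model type and the loss of a formal test on tenure. The vocational durations are already collected in days, so only analysis wording changes. The change should be made before unblinded analysis.
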